## Abstract

**Background:**

Peripartum cardiomyopathy (PPCM) is an idiopathic heart disease that develops in the last month of pregnancy and/or the first months following delivery in previously healthy women and may lead to acute heart failure. A cleaved fragment of the nursing hormone prolactin is considered essential in the pathophysiology of PPCM. To date, no specific therapy has been tested for PPCM in a randomized controlled trial of adequate size.

**Aims:**

The purpose of this trial is to investigate the safety of the dopamin-D2-receptor agonist bromocriptine and its effects on left ventricular (LV) function in women with PPCM.

**Methods:**

This is an 11 center German trial with a prospective randomized controlled open-label design. The trial enrolls females with newly diagnosed PPCM according to European Society of Cardiology criteria with a LV ejection fraction (LVEF) <35 %. Patients are randomized 1:1 to either best supportive care (BSC) including standard heart failure therapy plus 8 weeks of bromocriptine therapy (2.5 mg b.i.d. for 14 days and 2.5 mg q.d. from day 15 to 56) or to BSC plus 1 week of low-dose bromocriptine (2.5 mg q.d.) with anticoagulant therapy at a prophylactic dose administered during the period of bromocriptine treatment in both groups. The primary endpoint is change in LVEF from baseline to 6 months follow-up as assessed by cardiac magnetic resonance imaging (or echocardiography if CMR is not tolerated). The secondary endpoints are hospitalization for worsening heart failure, heart transplantation, and all-cause mortality during follow-up or a combination of these endpoints. A total of 60 patients will be recruited (including 6 potential dropouts) giving a power of 0.9 for an expected LVEF change of 10.8 % between treatment groups at 6 months.

**Perspective:**

This trial will provide important knowledge on potential benefits and safety of prolonged inhibition of prolactin release with bromocriptine in addition to standard heart failure therapy in newly diagnosed PPCM.

Trial registration: ClinicalTrials.gov Identifier: NCT00998556.

## Introduction

Peripartum cardiomyopathy (PPCM) is an idiopathic cardiomyopathy toward the end of pregnancy or in the months following delivery presenting with acute heart failure with reduced left ventricular (LV) function [1, 2]. The incidence of PPCM ranges from 1:299 births in Haiti to about 1:1000 in South Africa and in the USA [2, 3].

Moreover, recent studies suggest a growing incidence of PPCM [3] which may be partly due to certain socio-environmental factors that still need to be identified and partly due to improved awareness to this disease and advances in diagnostic opportunities.

Although PPCM is presumed to be associated with a higher likelihood of recovery of LV function than other cardiomyopathies [4], we recently reported on 15 % treatment failure in a German registry with prospective data of 96 PPCM patients despite optimal medical therapy.

The disease is potentially life threatening with regionally varying mortality rates ranging between 2 % in our registry under contemporary management concepts, and up to 50 % in other studies [5–7].

Importantly, a number of studies on PPCM cohorts of different ethnicities have demonstrated that the presence of severe LV dysfunction at baseline is associated with a low probability of full cardiac recovery [5, 8]. Among the triggering factors the nursing hormone prolactin is considered to play a key role in the pathophysiology of (PPCM). Under circumstances of enhanced oxidative stress that typically occurs toward the end of pregnancy and during delivery, prolactin is increasingly cleaved into a 16 kDa fragment (16 kDa PRL) under conditions of defective antioxidative mechanisms [9]. The 16 kDa PRL is known to exert detrimental effects on the microvasculature of the heart leading to cardiac injury and dysfunction [9, 10].

Despite these advances in understanding the pathomechanisms of PPCM, clinical trials testing disease-specific therapeutics still remain scarce. In fact, apart from standard heart failure medication no specific therapy is available for PPCM to date.

Thus, there is a need for new therapeutic strategies to counteract the detrimental pathomechanisms in PPCM and enhance myocardial recovery. Given the key role of prolactin in the pathogenesis of PPCM, prolonged inhibition of prolactin release by the dopamin-D2-receptor agonist bromocriptine may represent one therapeutic opportunity. After this approach had been successfully tested in single cases [11], a prospective, single-center, randomized, open-label, pilot study of African women with newly diagnosed PPCM was performed which compared standard heart failure care in PPCM patients versus standard care plus treatment with bromocriptine for 8 weeks with 10 patients per group (Table 1) [12].

Patients receiving bromocriptine displayed greater recovery of ejection fraction at 6 months and were less likely to experience the composite end point of poor outcome defined as death, New York Heart Association (NYHA) functional class III/IV, or left ventricular ejection fraction <35 % at 6 months than the patients receiving standard care. One patient in the bromocriptine group died compared with 4 patients in the standard care group. Although of limited small size, this trial justified the concept of targeting prolactin as a novel therapeutic strategy for PPCM and provided the rationale for a larger randomized and controlled clinical trial with bromocriptine (Table 1). This concept was further supported by the results of the German PPCM registry [5] demonstrating cardiac improvement in 96 % of the patients receiving bromocriptine in a non-randomized manner in addition to a beta-blocker and angiotensin-converting enzyme (ACE-) inhibitors (Table 1).

**Table 1 Tab1:** Summary of published studies investigating bromocriptine in patients with PPCM

Study	Sample size (*n*)	Treatment duration	Randomized?	Controlled?	Endpoint
Sliwa et al. [12]	20	8 weeks	Yes	Yes	LVEF at 6-month follow-up
Haghikia et al. [5]	96	4 weeks	No	No	LVEF at 6-month follow-up

Thus, the objective of the present study is to determine in a randomized and controlled design and with adequate sample size the therapeutic potential and safety of bromocriptine in patients with acute heart failure and reduced LV function due to newly diagnosed PPCM.

## Study design

This study is a prospective, randomized, controlled trial, which is conducted in 11 centres in Germany (Fig. 1).

**Fig. 1 Fig1:**
[figure not shown]
Study design. * Asterisks* indicates anticoagulation therapy at prophylactic dose is administered during treatment with bromocriptine.

## Eligibility

The inclusion and exclusion criteria are summarized in Table 2. The aim is to enroll patients with newly diagnosed PPCM in accordance to the definition proposed by the Working Group on PPCM from the Heart Failure Association of the European Society of Cardiology (ESC) [1] which is as follows: (a) evidence of heart failure secondary to systolic dysfunction toward the end of pregnancy or in the months following delivery, where no other cause of heart failure is found; (b) it is a diagnosis of exclusion; (c) the left ventricle may not be dilated but the ejection fraction is nearly always reduced below 45 %.

**Table 2 Tab2:** Summarized inclusion and exclusion criteria

Inclusion criteria	Exclusion criteria
Confirmed PPCM according to ESC definition Time-window within 5 months postpartum LVEF ≤35 % At least 18 years of age Ability to give written informed consent	Preexisting cardiac disease (except PPCM with complete resolution) Any preexisting serious conditions Previous cardiac surgery or percutaneous coronary intervention History of alcohol and/or any other drug abuse Contraindication to the planned therapy Concomitant therapy other than specified in the trial protocol Expected low compliance (e.g., by travel distance to trial site) Concomitant participation in other clinical trials

*ESC* European Society of Cardiology, *PPCM* peripartum cardiomyopathy, *LVEF* left ventricular ejection fraction

Specific inclusion criteria include (1) the confirmed diagnosis of new onset PPCM within a time-window of 5 months postpartum; (2) LV ejection fraction (LVEF) below 35 % as assessed by echocardiography; (3) the age of 18 years or older; and (4) the ability to give written informed consent. PPCM is defined as a non-familial form of peripartum heart failure characterized as an “idiopathic cardiomyopathy presenting with heart failure secondary to left ventricular (LV) systolic dysfunction towards the end of pregnancy or in the months following delivery, where no other cause of heart failure is found”.

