## Registration, screening, enrolment, and randomization

### Registration and screening

Potential participants are all women with PPCM in the first 5 months postpartum displaying clinical signs of heart failure. After explanation of the nature and scope of the study and a sufficient period of reflection, the investigator must obtain the informed consent by means of a standard written statement in non-technical language. Patients may withdraw their consent of participation at any time of the trial without providing a reason. Patients with heart failure symptoms are screened for PPCM by echocardiography and further inclusion and exclusion criteria are evaluated during the enrolment and randomization visit (visit 1).

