### Enrolment and randomization (visit 1)

At visit 1, patient eligibility is evaluated based on the inclusion/exclusion criteria (Table 2). If the patient is considered eligible, the medical history is assessed, physical examination, ECG, and echocardiography are performed and the NYHA class and vital signs are documented. The baseline LVEF has to be determined by cardiac magnetic resonance imaging (CMR) within 5 days after beginning of bromocriptine therapy. Alternatively, if the patient does not tolerate CMR or CMR is temporarily not available, it may as an exception be replaced by two separate echocardiograms with determination of the LVEFs (Simpson’s method) by two independent investigators blinded to each others results. Moreover, laboratory tests for NTproBNP, hemoglobin, serum sodium and potassium, glucose, aspartate aminotransferase, alanine aminotransferase, total bilirubin, blood urea, nitrogen, and serum creatinine are measured. The quality of life is assessed by means of a questionnaire.

Patients who are not eligible to participate in the study are asked to provide their demographic (age, parity, ethnic background) and clinical data for the German PPCM registry [5] and the international registry on PPCM, which is part of the ESC EURObservational Research Programme (http://www.eorp.org) [13].

A central computerized randomization (modified according to Pocock 15 and Pocock and Simon 16) of patients fulfilling the inclusion criteria is performed at the Coordination Centre for Clinical Trials at the University of Leipzig (ZKS Leipzig KKS). Patients are randomized in a 1:1 ratio to either the treatment group or the control group. The treatment group receives bromocriptine therapy at a dose of 2.5 mg b.i.d for the first 2 weeks and 2.5 mg o.d. for another 6 weeks (total treatment of 8 weeks with bromocriptine). The control group receives low-dose bromocriptine (2.5 mg o.d.) for up to 1 week to stop lactation. In both groups anticoagulant therapy at a prophylactic dose is administered during the period of bromocriptine treatment to prevent thrombotic side effects of bromocriptine.

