### Statistical consideration

The estimated average change of LVEF during 6 months for the primary endpoint was based on the previous pilot study including 10 patients with and 10 patients without bromocriptine where the average change of LVEF during 6 months was by absolute 23 % higher in the group with bromocriptine [12]. We assume that the average difference between the groups in this study is 12 % absolute, corresponding to a 52 % relative reduction of the effect seen in the pilot study. If we assume that the patients in the control group who receive 1/10 of the cumulative dose given to the patients of the treatment group might have 1/10 of the benefit, this will reduce the average gain in LVEF to 10.8 % in absolute terms with a standard variation of 12 %. Consequently, to detect this difference in a two-sided difference test with a type I error level of 0.05 and a power of 0.9, a total of 54 patients is needed, 27 per group. Therefore, a total of 60 patients (30 per group) should be sufficient to allow for 3 dropouts per group. Regarding the primary endpoint, an analysis of covariance will be performed. The follow-up LVEF will be defined as dependent variable, the treatment group as fixed factor and the baseline LVEF as covariate. As for the secondary endpoints, frequency tables of rates with appropriate 95 % confidence intervals will be performed and comparisons using contingency tables will be compiled. If sufficient numbers of events occur, additional time-to-event analyses, such as Kaplan–Meier estimates of survival curves, will be carried out.

A final detailed plan for the statistical analyses will be developed prior to the end of study and the start of the final analysis.

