The design of this study has been encouraged by a previous pilot study [12] and the findings of the non-randomized German PPCM registry [5] indicating beneficial effects of bromocriptine on LV function in PPCM. However, the current study is not fully comparable with the study be Sliwa et al. [12], which was placebo controlled as opposed to our study which compares low-dose short-term treatment of bromocriptine with prolonged bromocriptine treatment. This study design was based on ethical concerns about the continuation of lactation despite treatment of the patients with heart failure medication with potential side effects for the newborn, and because of the strong therapeutic effect of bromocriptine in the pilot study. Moreover, our ethic committee pointed out that stopping lactation without offering medical support is not allowed in Germany. The rationale for this treatment concept is based on experimental and clinical observations that a cleaved form of the nursing hormone prolactin, the 16 kDa prolactin, plays a causal role in the development of PPCM [9, 12]. This cleaved peptide exerts strong angiotoxic effects, in particular on the microvasculature, ultimately leading to cardiomyocyte cell death, and fibrosis. This hypothesis is supported by the evidence of increased serum levels of 16 kDa prolactin and augmented activity of the cleaving enzyme, cathepsin D [5, 12], at baseline in PPCM patients as compared to postpartal healthy women. Therefore, early pharmacological blockade of prolactin with bromocriptine may eliminate the detrimental effects of 16 kDa prolactin, prevent damage of the microvasculature, cell death, and replacement fibrosis, and thus, avoid adverse remodeling of the diseased myocardium and improve cardiac function and clinical condition of patients with acute onset of PPCM [9, 12]. Moreover, additional pleiotropic effects of bromocriptine are assumed to contribute to the healing process of the injured myocardium in PPCM. For example, proinflammatory pathways are known to be involved in the pathophysiology of PPCM [8, 23], which appear to be modulated upon treatment with bromocriptine [9, 23]. Further studies are warranted to identify precise mechanisms by which bromocriptine modulates the immunological responses that are activated in the development of PPCM. Other beneficial effects that have been attributed to bromocriptine are potential cytoprotective and antioxidative capabilities that could compensate for defective antioxidative mechanisms proposed as an important pathophysiological aspect in PPCM [8, 9]. Taken together, the cardioprotective effects of bromocriptine are broader than just effective prolactin blockade.

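### The primary ANCOVA is valid but leaves out time from delivery to randomisation, a plausible predictor of recovery already needed for eligibility; adding it could gain a little precision at almost no cost

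*Protocol article*

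**What the plan says.** Under Eligibility, the protocol article requires "the confirmed diagnosis of new onset PPCM within a time-window of 5 months postpartum". Registration and screening describes the same population: "Potential participants are all women with PPCM in the first 5 months postpartum displaying clinical signs of heart failure". The article describes no narrower window and no stratum by time since delivery. The window is one of the criteria in Table 2, which are applied to every woman at enrolment: "At visit 1, patient eligibility is evaluated based on the inclusion/exclusion criteria (Table 2").

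The Discussion gives the reason for treating: "early pharmacological blockade of prolactin with bromocriptine may eliminate the detrimental effects of 16 kDa prolactin". It goes on to say that this would prevent microvascular damage, cell death and fibrosis.

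Statistical consideration writes the primary model out: "The follow-up LVEF will be defined as dependent variable, the treatment group as fixed factor and the baseline LVEF as covariate". No other covariate is named. The same section announces a detailed analysis plan, to be written before the study ends; that plan is not at hand. Allocation uses a central method modified from Pocock and Pocock-Simon, and the article does not name the balancing factors.

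**The concern.** If benefit depends on blocking prolactin before damage is done, a woman randomised a few days after delivery and one randomised near five months may differ in how much recovery lies ahead. That would make time since delivery a prognostic variable for month-6 LVEF. It is fixed before randomisation, treatment cannot affect it, and the trial must already know it to apply the entry window. A model without it leaves whatever it explains in the error term.

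What is at stake is precision in a small trial. The plan needs 27 evaluable women per group and allows for three losses in each. Current status already reports six dropouts after randomisation among 49 enrolled, although the intention-to-treat analysis may keep some of them. A cheap gain in precision is therefore worth having.

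Because the article states the model and its covariate, this is a comment on a stated choice, not on a detail left to the analysis plan.

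**Working it through.** **Inputs from Statistical consideration.** Difference 10.8 LVEF points, SD 12, two-sided alpha 0.05, power 0.90, 27 evaluable per group.

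**Assumption.** The article gives no figure for how strongly time since delivery predicts month-6 LVEF. R² below is the assumed share of residual variance that it explains, shown over a range. The SD of 12 is taken as the residual SD before time is added.

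**Step 1: the plan's own figure.** Standard error of the difference = 12 × √(2/27) = 3.266. Noncentrality = 10.8 / 3.266 = 3.307. The two-sample t-test on 52 degrees of freedom has power 0.9006 at 27 per group and 0.8892 at 26. So 27 per group (54 in total) reproduces.

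**Step 2: add the covariate.** Residual SD = 12 × √(1 − R²), with one further degree of freedom spent (51).

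| Assumed R² | Residual SD | Standard error | Power at 10.8 points | 95 % CI half-width |
|---|---|---|---|---|
| 0 | 12.00 | 3.266 | 0.9004 | 6.56 |
| 0.05 | 11.70 | 3.183 | 0.914 | 6.39 |
| 0.10 | 11.38 | 3.098 | 0.928 | 6.22 |
| 0.20 | 10.73 | 2.921 | 0.952 | 5.86 |

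Charging another degree of freedom for baseline LVEF (50 in all) changes the power figures by no more than 0.0002.

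**Step 3: a smaller true effect.** At a true difference of 8 points, power is 0.67 with R² = 0, 0.72 with R² = 0.10 and 0.77 with R² = 0.20.

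**Step 4: chance imbalance is the same quantity.** Under simple randomisation, an imbalance of one standard error in time since delivery moves the unadjusted estimate by √R² × 3.266, which is 1.03 points at R² = 0.10. In variance terms, 3.266² − 3.098² = 10.67 − 9.60 = 1.07, and √1.07 = 1.03. The shift is exactly the part of the standard error that adjustment removes. It is already covered by the planned test and confidence interval, and must not be counted as a second cost. It would be smaller if time since delivery is one of the unnamed balancing factors.

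**Step 5: what a main effect cannot answer.** A main-effect covariate does not test whether earlier treatment works better. For an interaction between early and late halves (median split), the standard error is 2 × 3.266 = 6.53. An interaction of 10.8 points gives 10.8 / 6.53 = 1.65, and Φ(1.65 − 1.96) is about 0.38.

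**The case against.** The strongest reply is that nothing here is wrong. ANCOVA of follow-up LVEF on treatment and baseline LVEF is a standard, valid analysis of a randomised trial, the sample size is correct without a further covariate, and the announced analysis plan may add one. All of that stands. It limits the point to an improvement and does not remove it, because the model is written out and can still be amended.

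Second, early in the Discussion may mean early after disease onset. The article speaks there of acute onset and enrols newly diagnosed disease. A woman whose disease begins four months after delivery may be treated early, while one whose symptoms began in late pregnancy may be treated later in her illness. Time since delivery is therefore only a proxy, and the article nowhere reports that it predicts recovery. The predictor that the Introduction does name, severe LV dysfunction at baseline, is addressed by the baseline LVEF term. This stands, and is why R² is shown as a range that includes zero.

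Third, that the value is known for every woman is inferred from the eligibility check; the article does not list it as a recorded variable. The inference is safe, since the window cannot be applied without it.

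A reader might go further than the article allows in three ways:

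- One might infer that the estimate is biased, or that chance imbalance in timing is a harm beyond lost precision. Randomisation rules out the first and Step 4 the second.
- One might infer that the size of the imbalance does not depend on the allocation factors. It does, and they are not named.
- One might infer that baseline LVEF is a weak covariate because entry is restricted to low values. The entry limit applies to echocardiography, whereas the baseline for the endpoint is normally measured by CMR and is not itself cut off at 35 %. The article gives no figure to support the claim.

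**Conclusion.** The point holds as a minor matter of efficiency. The planned ANCOVA is valid and 27 per group is correct. Adding time from delivery to randomisation would raise power at 10.8 points by about 1 to 5 percentage points if it explains 5 % to 20 % of the residual variance, and would narrow the confidence interval half-width from 6.56 to between 6.39 and 5.86 points. If it explains nothing, the cost is 0.0002 in power. The gain rests wholly on the assumed R², for which the article offers a rationale but no data. The case for acting is that the downside is negligible, not that a large gain is shown.

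**What to change.** Before the final analysis, and before follow-up LVEF is examined by treatment group, the analysis plan should add time from delivery to randomisation as one continuous covariate in the primary ANCOVA. Its functional form should be fixed at the same time. A log scale should not be adopted by default, because it gives high leverage to women randomised within days of delivery. The model with treatment and baseline LVEF only should be kept as a sensitivity analysis. If a treatment-by-time interaction is reported, it should be labelled exploratory, since it has about 38 % power even for a 10.8-point difference between early and late halves.

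The cost is a sentence or two in the plan and one degree of freedom. No new data should be needed, because the delivery date is required for eligibility. The sample size does not change.
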